### Sample size

2.3

The sample size was calculated to detect meaningful differences in gross motor competence between the intervention and control groups, while accounting for the cluster-randomized design. Previous intervention trials and meta-analyses of preschool motor-skill programs have consistently reported large effect sizes, often exceeding 1.0, for improvements in fundamental motor skills (7). Based on this evidence, we adopted an assumption of an effect size of 1.0 for between-group differences.

Using a two-tailed alpha of 0.05 and a statistical power of 80%, an individually randomized design would require approximately 21 children per group. Because this study uses class-level randomization, the required sample size was adjusted for clustering. Assuming an average class size of 25 and an intra-class correlation coefficient of 0.05, the design effect is estimated at 2.2. This adjustment results in an effective sample size of 46 children per group, or 92 children in total. To accommodate an anticipated dropout rate of 15%, we plan to recruit approximately 110 children overall, distributed across four to six kindergarten classes in Changsha city.

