### Statistical analysis

2.8

All analyses will follow the intention-to-treat principle, with all children analyzed according to their randomized class regardless of adherence or attendance. Descriptive statistics will be reported for baseline demographic and developmental characteristics, including age, sex, height, weight, and baseline TGMD-3 scores, to assess comparability between groups. Continuous variables will be summarized using means and standard deviations, while categorical variables will be summarized using frequencies and percentages.

For the primary outcome of gross motor competence, linear mixed-effects models will be used to examine group (intervention vs. control) by time (baseline vs. post-intervention) interactions, accounting for clustering at the class level. Models will include random intercepts for class and child, and fixed effects for group, time, and the group-by-time interaction. Relevant covariates, including age and sex, will be included where appropriate. Because the number of clusters (classes) in the present study is relatively small, degrees of freedom for fixed effects will be estimated using the Satterthwaite approximation within the linear mixed-effects modeling framework. This approach reduces potential underestimation of standard errors and helps control Type-I error rates in studies with limited cluster numbers.

For EEG outcomes, analyses will follow the pre-specified hierarchy of neural endpoints. The primary EEG analysis will focus on frontal theta power during resting state. A secondary task-related neural index will be the N2 amplitude elicited during the Go/No-Go task. Separate linear mixed-effects models will be constructed for each neural endpoint to evaluate group-by-time interactions, using the same clustering structure as described for the primary motor outcome (random intercepts for class and child).

Additional EEG measures will include spectral power indices in the alpha and beta frequency bands, which will be analyzed using similar mixed-effects models. To account for multiple comparisons across these secondary neural measures, false discovery rate adjustments will be applied. These analyses will be interpreted as supportive and contextual rather than confirmatory.

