Exploratory analyses will examine associations between changes in TGMD-3 scores and changes in EEG-derived neural indicators, as well as feasibility analyses of EEG recordings obtained during selected motor tasks. Correlational analyses will use Pearson or Spearman coefficients as appropriate, with regression models applied to adjust for relevant covariates. Results from exploratory analyses will be interpreted as hypothesis-generating.

Behavioral performance measures from cognitive tasks, including accuracy and reaction time, will be analyzed using mixed-effects models parallel to those used for neural indices. Questionnaire outcomes (BRIEF-P and SDQ) will also be examined using mixed-effects models to compare baseline-to-post changes across groups, adjusting for clustering.

Missing data for behavioral and questionnaire outcomes will be handled using maximum likelihood estimation within the linear mixed-effects modeling framework, which provides unbiased parameter estimates under the assumption of missing at random (MAR). This will serve as the primary approach to incomplete outcome data. The proportion and pattern of missingness will be examined descriptively. If missingness exceeds anticipated levels or suggests deviation from the MAR assumption, sensitivity analyses will be conducted to evaluate the robustness of findings.

All statistical tests will use a two-sided alpha level of 0.05. Analyses will be performed using SPSS 25.0 (IBM, Armonk, NY, USA).

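### Satterthwaite degrees of freedom do not correct standard errors, and in the planned group-by-time model they give no small-cluster protection if changes cluster by class

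*Protocol article*

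**What the plan says.** Section 2.3 of the protocol article plans about 110 children "distributed across four to six kindergarten classes in Changsha city", with an assumed average class size of 25 and an intra-class correlation (ICC) of 0.05.

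Section 2.8 tests "group (intervention vs. control) by time (baseline vs. post-intervention) interactions, accounting for clustering at the class level" for TGMD-3. The model is fixed: "Models will include random intercepts for class and child, and fixed effects for group, time, and the group-by-time interaction". The resting theta and N2 models use the same clustering structure, and the alpha and beta models are described as similar. Because classes are few, "degrees of freedom for fixed effects will be estimated using the Satterthwaite approximation", and the section adds: "This approach reduces potential underestimation of standard errors and helps control Type-I error rates in studies with limited cluster numbers".

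The missing-data paragraph of 2.8 says that incomplete behavioral and questionnaire outcomes will be "handled using maximum likelihood estimation within the linear mixed-effects modeling framework, which provides unbiased parameter estimates" under missing at random (MAR). REML is not mentioned. Questionnaires are to be analysed by "mixed-effects models to compare baseline-to-post changes across groups, adjusting for clustering". For the level: "All statistical tests will use a two-sided alpha level of 0.05".

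**The concern.** The document offers one safeguard against having few clusters, and it credits that safeguard with a property it lacks. Satterthwaite chooses the reference t distribution. It does not alter the standard error. If the standard error omits a source of variation, Satterthwaite neither restores it nor shows that it is missing.

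Two separate consequences follow.

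- **Planned group-by-time tests.** A class random intercept is constant over time, so it drops out of a baseline-to-post contrast. What matters for that contrast is whether classes differ in their average change, for instance because teachers differ. The planned model has no term for this.
- **Tests whose standard error does carry class variance.** Here the estimator matters. Full maximum likelihood (ML) underestimates class variance when there are few classes, and REML corrects for the fixed effects.

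At stake is whether the tests hold the stated two-sided 0.05.

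**Working it through.** **Inputs.** From section 2.3: four to six classes, ICC 0.05, class size 25, 92 children before the dropout allowance. The design effect reproduces: 1 + (25 - 1) × 0.05 = 2.2. Taking the stated 21 per group as given, 21 × 2.2 = 46.2, or 46 per group and 92 in total. Spread over classes, this is 23 per class with k = 4 (N = 92) and about 15 with k = 6 (N = 90). Assumed: normal data, equal class sizes, no covariates, complete pairs. The document gives no ICC for change scores, so 0.05 is carried over as an assumption and varied.

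**Step 1: the planned group-by-time test.** With two time points and complete data, the test compares mean change between arms. Let ρ be the change-score ICC and m the class size, with total variance of change set to 1.

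- True variance of a class mean change, times m: λ = 1 + (m - 1)ρ.
- Variance the model uses (change pooled over children, N - 2 df), in expectation: [(k - 2)λ + (N - k)(1 - ρ)] / (N - 2).

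At ρ = 0.05:

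| | k = 4, m = 23 | k = 6, m = 15 |
|---|---|---|
| λ | 1 + 22 × 0.05 = 2.10 | 1 + 14 × 0.05 = 1.70 |
| Model variance | (2 × 2.10 + 88 × 0.95)/90 = 0.976 | (4 × 1.70 + 84 × 0.95)/88 = 0.984 |
| True SE / model SE | √(2.10/0.976) = 1.47 | √(1.70/0.984) = 1.31 |
| Critical value (N - 2 df) | 1.987 | 1.987 |
| Approximate error, 2[1 - Φ(1.987/ratio)] | 17.6% | 13.1% |

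Simulation with 1,000,000 null trials per cell:

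| Change-score ICC | k = 4: ML / REML | k = 6: ML / REML |
|---|---|---|
| 0 | 5.3% / 5.0% | 5.3% / 5.0% |
| 0.01 | 7.9% / 7.6% | 6.9% / 6.6% |
| 0.05 | 18.4% / 17.9% | 13.9% / 13.4% |
| 0.10 | 28.8% / 28.2% | 21.6% / 21.1% |

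The two estimators differ by less than 0.6 point throughout, so the inflation comes from the missing term and not from the estimator.

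**Step 2: a test that does carry class variance**, such as a change-score model with a class random effect. When the class variance estimate is positive, ML divides the between-class sum of squares by k where REML divides by k - 2. The ML standard error is therefore √[(k - 2)/k] of the REML one: √(2/4) = 0.71 for four classes and √(4/6) = 0.82 for six. These 29% and 18% shortfalls are limits that apply when class variance dominates. At ICC 0.05 the estimate is often zero, so simulation is needed:

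| ICC 0.05 | k = 4 | k = 6 |
|---|---|---|
| ML, Satterthwaite df | 11.9% | 8.4% |
| REML, Satterthwaite df | 6.7% | 4.9% |
| Class-level test, k - 2 df | 5.0% | 5.0% |

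The ML row is sensitive to assumptions. It is about 4% to 5% at ICC 0 and about 10% to 16% at ICC 0.10. At ICC 0.05 it falls to 4.8% to 6.5% if class-level degrees of freedom are kept when class variance is estimated as zero.

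**The case against.** The strongest reply has four parts.

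**The ML sentence concerns missing data.** It sits in the missing-data paragraph, its claim of unbiasedness is tied to MAR, and it does not mention EEG. It may mean likelihood-based handling in general, and the choice between ML and REML is often left to an analysis plan. This stands: full ML is a fair reading but not a certain one.

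**The 8% to 12% is not the trial's error rate.** A reader might infer that ML makes the primary TGMD-3 test run at 8% to 12%. The document does not support that. In the specified model class variance cancels and ML costs about 0.3 to 0.5 point. The figure fits at most one reading of the questionnaire analysis, which is supplementary and could equally be a group-by-time model like the others.

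**Naming REML would repair little.** This also stands for the planned tests. Step 1 shows that REML leaves their inflation almost untouched.

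**Controlling type I error is a reasonable aim for a degrees-of-freedom method, and the wording is hedged.** This is true in general. It does not rescue the claim about standard errors, which is wrong as stated. Nor does it help where the degrees of freedom are child-level, as they are for the tested contrast.

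The document does not show that changes cluster by class. With no clustering of change, the planned test is close to 5%.

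**Conclusion.** The concern holds in a limited form. It is certain that Satterthwaite does not reduce underestimation of standard errors, and that in the specified model it gives no few-cluster protection to the group-by-time tests of TGMD-3 and EEG. Whether that matters depends on an unstated quantity. Type I error is about 5% with no clustering of change, and about 13% (six classes) to 18% (four classes) at an assumed change-score ICC of 0.05, under either estimator.

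The ML point is secondary and conditional. It needs full ML to be meant, a test whose standard error carries class variance, an ICC near 0.05, and child-level degrees of freedom when class variance is estimated as zero. Under those conditions the error is about 8% to 12%, against 5% to 7% with REML.

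This should be corrected before analysis. It concerns the stated basis for inference on the primary outcome, and section 4 of the article puts the start of analysis at September 2026.

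**What to change.** In section 2.8:

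1. Delete the statement that Satterthwaite reduces underestimation of standard errors.
2. State that the mixed models are fitted by REML, with the MAR handling unchanged.
3. Test the group effect on change so that class-level variation in change enters the standard error. Either analyse class-level change on k - 2 degrees of freedom, or add a class-by-time random effect with REML and Kenward-Roger or k - 2 degrees of freedom. Apply the same rule to EEG and questionnaire outcomes.

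The class-level analysis is the simpler choice and holds 5.0% in simulation. If the mixed model is kept with k - 2 degrees of freedom, it is conservative when class variance is estimated as zero: 0.2% (four classes) and 1.8% (six) at ICC 0.05. If Kenward-Roger is chosen, confirm that the named software version offers it.

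The change needs a few sentences and no new data. The price is precision. With the standard error √(2λ/n), n per arm, in SDs of change, it is √(2 × 2.10/46) = 0.302 for four classes and √(2 × 1.70/45) = 0.275 for six. The critical values are 4.303 (2 df) and 2.776 (4 df), so 95% half-widths are 1.30 and 0.76 SD. The planned model would report about 1.987 × √(2 × 0.976/46) = 0.41 and 1.987 × √(2 × 0.984/45) = 0.42. If the effect of 1.0 is read in SDs of change, power from the noncentral t (noncentrality 1/0.302 = 3.31 and 1/0.275 = 3.64) is about 44% with four classes and 78% with six. The number of classes therefore deserves attention when this wording is changed.

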## Discussion

3

This trial is designed to evaluate whether a structured motor-focused physical education program improves gross motor competence and is associated with concurrent changes in functional neurodevelopmental indicators in preschool children. While previous research has consistently demonstrated improvements in gross motor skills following structured motor interventions, less is known about how such training relates to functional brain activity during early childhood. By integrating portable EEG measures within a cluster-randomized design, the present study seeks to examine behavioral and neurodevelopmental outcomes within the same experimental framework.

A major strength of this trial lies in its ecological validity. The intervention will be delivered in real-world kindergarten classrooms by regular teachers using standardized lesson materials, enhancing the practical relevance of the findings. The use of cluster randomization, blinded motor assessments, structured fidelity monitoring, and predefined neural endpoints strengthens internal validity while maintaining feasibility in educational settings. The inclusion of EEG measures allows the examination of functional neural indicators associated with executive and attentional processes; however, these measures are intended to complement behavioral findings rather than to establish definitive mechanistic explanations.

The trial incorporates multiple levels of outcome assessment, including standardized motor testing (TGMD-3), neurophysiological indices, and ecologically valid parent- and teacher-reported measures. This multi-method approach permits examination of whether behavioral improvements in motor competence are accompanied by changes in functional indicators of self-regulatory processes. Nevertheless, neural findings will require cautious interpretation. EEG markers such as frontal theta activity and N2 amplitude are developmentally interpretable within early childhood research, but they do not provide direct evidence of structural brain change or long-term neurodevelopmental modification.

Several limitations warrant consideration. First, although portable EEG enables assessment in preschool environments, recordings are inherently vulnerable to movement artifacts and compliance challenges. Despite standardized preprocessing and artifact rejection procedures, some data loss is anticipated. Second, while the study is powered to detect large effects on the primary behavioral outcome, it is not powered for definitive inference regarding neurophysiological endpoints. Accordingly, EEG analyses should be interpreted as exploratory and hypothesis-generating. Third, the intervention duration is limited to one academic semester within a single regional context, and longer-term developmental trajectories cannot be inferred from the present protocol.

Despite these limitations, this study has the potential to make several important contributions. It will provide one of the first randomized controlled trials to integrate EEG into the evaluation of early motor-focused physical education, thereby linking behavioral and neural outcomes in a developmental framework. It will also generate practical insights for educators and policymakers by identifying not only whether motor-focused programs are beneficial, but also how they exert their influence on the developing brain. Ultimately, this knowledge may inform the design of optimized physical education curricula that promote both motor competence and cognitive readiness in young children, with long-term implications for academic achievement, physical activity participation, and health across the lifespan.

Within these boundaries, the study aims to contribute incremental evidence to the growing literature linking motor development and neurocognitive functioning in early childhood. The findings are intended to clarify whether structured motor-focused programs are associated with concurrent functional neural indicators during a sensitive developmental period. If such associations are observed, they may inform future research examining scalable approaches to support early developmental trajectories within educational settings.

## Ethics and dissemination

4

This study protocol has been reviewed and approved by the Ethics Committee of Hunan Normal University (approval number: 2025-532). All procedures will be conducted in accordance with the ethical principles outlined in the Declaration of Helsinki. The trial has been prospectively registered at ClinicalTrials.gov (identifier: NCT07307742, date of registration: December 26, 2025).

Written informed consent will be obtained from the parents or legal guardians of all participating children, and assent will be sought from children in an age-appropriate manner. Participation is voluntary, and families may withdraw at any time without penalty. Data confidentiality will be strictly maintained by assigning anonymized codes to all participants and storing information on secure, password-protected servers. Only the research team will have access to the data.

The risks associated with participation are minimal. Structured physical education activities are age-appropriate, consistent with typical preschool play, and will be supervised by trained teachers. EEG recording is non-invasive and will be conducted in a child-friendly manner to minimize discomfort or fatigue. The expected benefits include improvements in children's motor competence and developmental experiences, as well as contributions to advancing scientific knowledge.

Recruitment is expected to begin in March 2026 and continue until June 2026. Baseline assessments and randomization will take place immediately after enrollment, with the 16-week intervention phase running from March to July 2026. Post-intervention assessments are scheduled for July–August 2026. Data analysis will begin in September 2026, and the first results are anticipated for dissemination in late 2026 or early 2027.

Findings from this trial will be disseminated through peer-reviewed publications, presentations at national and international conferences, and lay summaries prepared for participating schools and families. Results will also be shared with local education authorities and policy stakeholders to inform evidence-based recommendations for early childhood physical education.
